## 2. Materials and Methods

### 2.1. Setting and Design

This study was approved by the Ethics Committee of the University Hospital Fundación Jiménez Díaz. Participants—when they are over 18 years old—or their legal tutors—when they are underaged—will give informed consent to participate in the study. Participants will not receive any financial incentive to become involved in the project.

This is a multicenter randomized clinical trial taking place in various clinical and educational settings across in Spain. Participants will be randomly assigned to either the intervention group, which will receive the digital safety plan on their mobile phone, and a control group. All participants will receive the continuous assessment through an EMA (also contained in the MEmind app, version 1.0). 

All participants will receive their usual treatment (Treatment As Usual, TAU), if they were doing so previously. Participants will be followed-up at 6 months.

### 2.2. Sample

Our study will be composed of three cohorts of participants recruited in different settings. 

#### 2.2.1. Cohort 1: Clinical Setting 

The clinical sample will consist of adolescents with a history of recent suicidal behavior or NSSIs—in the month before recruitment—seen in the emergency department, in the mental health hospitalization unit, or in the mental health outpatient clinics of seven hospitals located in the three Spanish regions of Madrid, Andalusia, and Asturias. 

The inclusion criteria for this group are: Being between 13 and 17 years old.Presenting a suicide attempt or an NSSI in the month previous to recruitment.Being able to understand the project and being interested in participating.Having parents or legal guardians capable of signing the informed consent.Being fluent in Spanish.Owning a smartphone with internet access and iOS or Android operating system.

The exclusion criteria for this group are:Refusal to install the mobile application.Any circumstance or indication that discourages the regular use of a mobile phone (e.g., addiction to new technologies).

#### 2.2.2. Cohort 2: High School

The high school sample will consist of adolescents aged 13 to 17 from ten secondary schools in the city of Madrid.

The inclusion criteria for this group are:Being between 13 and 17 years old.Testing positive in the screening that will be carried out at the centers (explained below).Being able to understand the project and being interested in participatingHaving parents or legal guardians capable of signing the informed consent.Being fluent in SpanishOwning a smartphone with internet access and iOS or Android operating system.

The exclusion criteria for this group are:Refusal to install the mobile application.Any circumstance or indication that discourages the regular use of a mobile phone (e.g., addiction to new technologies).

#### 2.2.3. Cohort 3: University Setting

This sample will consist of university students aged 18 to 24 at the University of Zaragoza.

The inclusion criteria:Testing positive in the screening that will be carried out at the center (explained below).Being able to understand the project and being interested in participating.Being capable of signing the informed consent.Being fluent in Spanish.Owning a smartphone with internet access and iOS or Android operating system.

The exclusion criteria:Refusal to install the mobile application.Any circumstance or indication that discourages the regular use of a mobile phone (e.g., addiction to new technologies).

### 2.3. Sample Size Calculation

Sample size calculation will be performed using G*Power software, version 3.1. Based on previous clinical trials that explore the ability of interventions in SI reduction, in the midterm [36] we estimate an effect size of 0.5. Since the alpha error is set at 5% and the power at 95%, performing the modality “Means: Difference from constant (one sample case)”, the program determined that we would need a minimum of 45 participants per branch. Considering our recruitment capacity and assuming dropouts, we set the sample size at 60 participants per branch (120 in total). In order to stratify by center—so that we can explore the possibility of bias by different recruitment centers—we will try to have this sample size in each of the participating hospitals as well as in the educational contexts, which would result in a total sample of 120 × 9 = 1080 participants.

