## 1. Introduction

Adolescence is a complex time in life when the risk of developing mental health problems increases. Age-specific risks, the acquisition of social roles, and the search for individuation and connection to peers may lead to social insecurity, feelings of uncertainty and increased influence of the peer group on behavior [1,2]. Some authors suggest that the concept of adolescence should be extended to 18–24 years of age (the range commonly known as young adulthood) because people in this group share neurobiological characteristics with people aged 13–18 [3]. Comparing the psychopathology of both groups could shed light on this debate. While concern about adolescent mental health is by no means a new concept, worries have intensified since the COVID-19 pandemic, as an increase in the range of mental health problems, including a spike in Non-Suicidal Self-Injuries (NSSI), has been reported [4].

Among the many mental health problems that can affect young people, suicidal behavior and Non-Suicidal Self-Injury (NSSI) are receiving growing attention due to the dramatic increase observed in recent years [5]. Suicide is the second leading cause of death among people aged 10–24 years old [6], and suicide attempts impose a significant financial burden on health care systems [7]. In 2000, suicide represented 8.5% of the total deaths in the 15–24 age group in Spain, and in 2021 this percentage raised to 15.8% [8]. With regard to NSSIs, not only does they increase the risk of suicide [9], but it is also associated with other mental health problems, such as emotional dysregulation or substance use [10].

Most research in suicide prevention in adolescents is conducted in clinical settings, providing a crucial look into patients at risk of suicide. In the mid- to long-term, the most important risk factor is a history of suicidal ideation or behavior. Therefore, individuals who previously attempted or considered suicide are at higher risk of suicide-related death [11]. Secondary prevention is thus a crucial area in preventing suicide deaths [12]. However, researching suicidal behavior in school settings is also important, as the rise of NSSIs is particularly alarming in schools. As part of the EPISAM-school study, suicide risk screening was carried out in schools in the community of Madrid, where it was found that 35% of young people had self-harmed, 12.6% were at risk of suicide and 5.7% had attempted suicide [2].

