### 2.8. Psychometric Assessment

The assessments will be carried out by a trained psychologist. The CSSRS [34] will be used to measure suicidal behavior and suicidal ideation. Sociodemographic data will also be collected, and a satisfaction survey will be carried out.

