### 2.12. Assessment Criteria

After six months, a before-and-after comparison will be made in both the control and intervention groups. 

Our main outcome will be a reduction in suicidal behavior, as measured by a score on the CSSRS.

Our secondary outcomes will be as follows: The occurrence of suicidal behavior as a clinical event (completed suicide, attempted suicide, ED visit for suicidal ideation, ED visit for self-harm),Predictive validity of the D/S IAT and SI IAT tests to clinical events recorded during follow-up.Acceptability of the project through user-perceived satisfaction.Project feasibility measured by participation and retention.

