## 4. Expected Results

This project is highly feasible, as the mobile application it uses has already been tested in previous studies in the adult population [35]. With this intervention, we hope to contribute to the mental health of the adolescent population in the following two ways: Firstly, by decreasing suicidal behavior over the course of follow-up, i.e., both suicidal ideation and suicide attempts, which will be reflected in lower CSSRS scores in the intervention group. Secondly, by reducing NSSIs through the acquisition of coping strategies that can be used in times of risk. This training should be a useful tool beyond the follow-up period of the study and could be applied in the long term. As NSSIs increase the risk of a subsequent suicide attempt, it is hoped that reducing NSSI episodes will also reduce suicide risk.

We also expect that The D/S IAT and SI IAT will demonstrate predictive validity with respect to the gold standard CSSRS.

Finally, we also expect the project to be well accepted by the participants, which will be reflected in the satisfaction surveys provided. Demonstrating its feasibility will allow it to be implemented on a large scale.

Monitoring will be a source of information for understanding suicidal behavior, NSSIs and their associated factors. Real-time monitoring will facilitate an individualized approach that will allow for the design of prevention strategies tailored to the uniqueness of each patient. 

Finally, it is important to stress the importance of transmitting to the adolescent population the need to seek help if they find themselves in a situation of suicidal risk. Given that this is a population that integrates mobile devices into their daily lives, it is expected that the demand for help will be more accessible; it is also hoped that the reception of the preventive approach will be improved.

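### The planning effect of 0.5 comes from trials of SI reduction, but the primary outcome is suicidal behaviour on an unnamed CSSRS score, so the 95% power belongs to no defined endpoint

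*Protocol article*

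**What the plan says.** - **Planning effect.** Section 2.3 bases the effect on "previous clinical trials that explore the ability of interventions in SI reduction" and states: "we estimate an effect size of 0.5". No scale, mean change or SD is given, and SI is not spelled out there. With alpha 5% and power 95% in a one-sample procedure, the section reports a minimum of 45 per branch. It raises this to 60 for dropouts and multiplies 120 by 9 to reach 1080.
- **Primary outcome.** Section 2.12: "Our main outcome will be a reduction in suicidal behavior, as measured by a score on the CSSRS". The subscale or score is not identified.
- **What the instrument covers.** Section 2.8 says the CSSRS "will be used to measure suicidal behavior and suicidal ideation". Section 2.11 likewise lists ideation and behaviour.
- **What the term covers.** Section 4 explains the expected fall in suicidal behaviour as a fall in "both suicidal ideation and suicide attempts", seen as lower CSSRS scores. The end of the Introduction links lower CSSRS scores to fewer episodes of both suicidal behaviour and NSSI.
- **Test.** Section 2.12 plans a before-and-after comparison in each group. Section 2.13 names t-tests between groups for continuous variables in general, but the only test it names for the CSSRS score is a Wilcoxon test of baseline against end of follow-up.
- **Entry.** The clinical cohort enters on an attempt or an NSSI in the past month (section 2.2.1). Students enter on a positive Paykel/ISAS screen (section 2.6), with no cut-off or combination rule given.

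**The concern.** A power statement holds only for the outcome whose effect size went into it. Here the effect was borrowed from SI trials. Appendix A uses SI under suicidality, for passive and active SI, which suggests ideation. Elsewhere SI labels the self-injury association test. On neither reading is it suicidal behaviour in the narrow sense, and the outcome wording does not say whether the narrow or the broad sense is meant.

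Two things are at stake. First, the 95% power cannot be attached to the primary analysis. Second, an ideation score, a behaviour score or a combination would each fit the text, so the choice could be made after the results are known.

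A conditional third issue follows. If a behaviour-only score is chosen, people who enter on NSSI or a screen alone may start at or near its floor and add little to a within-person test of reduction.

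**Working it through.** **1. The plan's own figure.** Inputs from section 2.3: d = 0.5, alpha 0.05, power 0.95, one-sample t-test.
- One-sided: n ≈ (1.645 + 1.645)² / 0.5² = 10.82 / 0.25 = 43.3. The exact noncentral-t answer is 45, which matches the article.
- Two-sided: (1.960 + 1.645)² / 0.25 = 52.0. The exact answer is 54, which does not match.
- Two arms, two-sided: 2 × 12.996 / 0.25 = 104. The exact answer is 105 per arm.

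So 45 is a correct one-sided, one-sample answer. That it does not suit a two-arm trial with two-tailed tests is a separate problem. Correcting the formula would not cure the present one, because every version still needs an effect size that belongs to the primary score.

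**2. How many scores fit.** Section 2.12 (suicidal behaviour by a CSSRS score), sections 2.8 and 2.11 (the CSSRS covers ideation and behaviour) and section 4 (behaviour includes ideation) together admit at least an ideation score and a behaviour score. A combination also fits. If either of two independent scores at 5% could be called primary, the chance of at least one false positive is 1 − 0.95² = 9.75%. With positively correlated scores it lies between 5% and 9.75%.

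**3. Possible floor, if the score is behaviour-only.** The Introduction reports for Madrid schools: "35% of young people had self-harmed, 12.6% were at risk of suicide and 5.7% had attempted suicide". Assume that these rates apply to cohort 2 and that every past attempter screens positive. The second assumption makes each share an upper bound.
- Any self-harm counts as positive: at most 5.7 / 35 = 16.3% of screen-positives have a past attempt.
- Self-harm or suicide risk counts, with no overlap: 5.7 / (35 + 12.6) = 12.0%.
- Only suicide risk counts: at most 5.7 / 12.6 = 45.2%.

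The Wilcoxon signed-rank test in its standard form drops zero changes, so participants who start and end at zero add little to it.

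**4. Effect on the pooled trial.** Assume seven hospital and two educational units, d = 0.5 in the hospitals, an unchanged SD, and a response in the educational units only among past attempters (12% to 16%). The pooled effect is 0.5 × (7 + 2 × 0.12) / 9 = 0.402 to 0.5 × (7 + 2 × 0.16) / 9 = 0.407. At 540 per arm, two-sided power stays near 1.00.

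**5. What the planned sample detects.** The planned sample is 1080 / 2 = 540 per arm. The dropout implied by 45/60 leaves 540 × 0.75 = 405.
- Continuous score, two-sided, 95% power: d = 3.605 × √(2/540) = 0.22, or 3.605 × √(2/405) = 0.25.
- Attempts, 10% v 5% (assumed rates), 540 per arm: SE = √[(0.10 × 0.90 + 0.05 × 0.95) / 540] = 0.0160; z = 0.05 / 0.0160 = 3.13; power = Φ(3.13 − 1.96) ≈ 0.88.
- The same at 405 per arm: SE = 0.0184; z = 2.71; power ≈ 0.77.

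**The case against.** The best defence is that the article uses suicidal behaviour broadly throughout. Section 4 includes ideation. The clinical-event outcome in section 2.12 includes emergency visits for ideation and for self-harm. The survival event in section 2.13 includes emergency visits for ideation. If SI means suicidal ideation and the CSSRS score includes it, the gap between planning effect and outcome narrows. The cited trials are not at hand, so the scale behind 0.5 cannot be checked. A fuller protocol or SAP may also name the score.

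This has force, but it does not close the gap. Even the broad reading leaves open whether the score is ideation, behaviour or both, and 0.5 is justified for none of them. Nor is this only a detail left to another document: the article's own sections use the term differently, and the power claim depends on which use is meant.

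A reader might go further and infer that most school and university participants cannot show the outcome at all. The documents do not support that:
- On the broad usage, a student with ideation and no attempt can improve.
- The screening cut-off and combination rule are unstated.
- The prevalence figures come from another study, in schools only, and say nothing about the university.
- CSSRS scoring is not described, so a zero start is an assumption.
- In a comparison between arms, a participant at zero still contributes if control participants worsen more often.

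A reader might also infer that 1080 is too few. Step 4 of the working does not show that, although its result depends on d = 0.5 in the hospitals, which is the premise in question.

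**Conclusion.** The point holds in limited form. The 0.5, and with it the 95% power, is not tied to a defined primary endpoint, and the wording admits at least two CSSRS scores. The false-positive rate could exceed 5% if the score were picked after the data are seen. The 9.75% is the value for two independent scores, not an estimate for this trial.

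The floor effect is a conditional risk. It needs a behaviour-only score, a within-person test, and school rates that carry over to cohort 2. Under those conditions at most about 16% (any self-harm positive) or 45% (suicide risk only) of school screen-positives would have a past attempt. No figure can be given for the university cohort, or for the NSSI-only share of the clinical cohort.

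The matter should be corrected before analysis. It does not show that the pooled trial is too small.

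**What to change.** - **Sections 2.12 and 2.13:** name one primary CSSRS score (ideation, behaviour or a stated composite), with the same recall window at baseline and six months. Compare it between arms instead of by a before-and-after Wilcoxon test. Make the other score secondary, and use suicidal behaviour in one sense throughout.
- **Section 2.3:** spell out SI and justify the effect size for the named score, including in screen-positive students. Otherwise withdraw the d = 0.5 power claim and state what the planned sample detects. If attempts are primary, an example is about 88% power for 10% v 5% at 540 per arm and about 77% at 405, with the rates marked as assumptions.

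The cost is mainly wording, with no change to recruitment or assessments. The choice of score does involve a trade-off. Ideation lies closer to the planning effect if SI means ideation, but it moves away from the main objective in the Introduction, which is to prevent suicidal behaviour and NSSI. Whichever score is chosen, the headline claim is tied to it and the stated power is likely to look less favourable.

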### 2.7. Randomization and Follow-Up

A 1:1 randomization will take place after enrollment, where each participant will be assigned to one of the two groups. In both the control and intervention groups, an initial visit will take place during which a psychiatrist or psychologist will install the MEmind app on the participants’ mobile phone so that they can answer the questionnaires contained in the app with the guidance of the evaluator. In the case of self-administered questionnaires, the participants will answer directly on the screen of their mobile phone. In the case of hetero-administered questionnaires, the evaluator will complete them via the MEmind web portal, which is synchronized with the application.

Participants will be followed for six months, with weekly and monthly telephone visits and face-to-face visits at three and six months. In the intervention group, participants will also be given access to the safety plan included in the MEmind application. During the baseline visit, the plan will be set up for the first time and how it works will be explained. 

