### 2.13. Statistical Analysis

Traditional statistical analyses will be performed using SPSS 25.0 statistical software. For continuous variables, we will use t-tests to compare means between groups and ANOVA for multiple group comparisons. For categorical outcomes, chi-square tests will be employed to examine the frequency distributions.

In order to compare suicidal behavior (CSSRS score) at baseline and at the end of follow-up, a Wilcoxon test will be used. Survival curves (time to a new event, defined as a completed suicide, a suicide attempt or a visit to the emergency room for suicidal ideation) will be calculated using the Kaplan–Meier actuarial method.

To assess the feasibility of the project, the participation rate and retention (by percentage and by survival curve using drop-out as an event) will be calculated. To assess the acceptability of the project, descriptive statistics will be provided for the quantitative satisfaction survey and a content analysis will be conducted for the qualitative satisfaction survey. Binary logistic regression will be used to explore the correlation between the study variables, obtaining crude ORs adjusted for age and sex. 

Additionally, to reduce the probability of bias, we will factor by certain variables that could potentially act as confounders, such as the presence of other health apps in the users’ phones and response latency (which will be measured). 

All tests will be two-tailed, with a significance level of *p* < 0.05 and 95% confidence intervals.

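### The 45 per branch in section 2.3 comes from a one-sample calculation, so its stated 95% power does not hold for the two-arm, two-tailed comparison; the pooled target of 1080 is nevertheless ample

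*Protocol article*

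**What the plan says.** All inputs to the sample size are in section 2.3 of the protocol article. The planning effect is standardised: "we estimate an effect size of 0.5". The error rates follow: "Since the alpha error is set at 5% and the power at 95" per cent. The G*Power option is named as "Difference from constant (one sample case", and the result is that "the program determined that we would need a minimum of 45 participants per branch". No number of tails is given. The figure is then raised to 60 per branch (120 in total), with recruitment capacity and dropout cited together and no dropout rate. The authors aim to repeat that unit in each participating hospital and educational context so that bias between centres can be explored: 120 × 9 = 1080.

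The design and analysis are described elsewhere in the article:

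- Section 2.7: "A 1:1 randomization will take place after enrollment, where each participant will be assigned to one of the two groups".
- Section 2.12: the main outcome is a reduction in CSSRS score, assessed before and after in each of the two groups.
- Section 2.13: t-tests for differences in means between groups, a Wilcoxon test of CSSRS at baseline against end of follow-up, and the general rule "All tests will be two-tailed".
- Section 4: CSSRS scores are expected to be lower in the intervention group.

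**The concern.** A one-sample calculation has no control arm. It carries the sampling error of one mean, while a comparison of two arms carries the sampling error of two. Calling its answer a per-branch figure therefore understates what a between-arm test needs. The expectation in section 4 is a between-arm claim, and no calculation in the article addresses it.

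The tail is a second mismatch. A one-tailed sizing sits beside an analysis section that makes every test two-tailed.

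At stake is a stated design property. The only power statement in the article is 95% at 45 per branch. That unit is carried into every setting, while the power of the pooled comparison, which the trial could deliver, is never given. The total of 1080 is worded as something the authors will try to reach. If recruitment fell far short, the documented justification would still say that 45 per branch is enough.

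**Working it through.** **Inputs.** From section 2.3: d = 0.5, alpha = 0.05, power = 0.95, 45 and 60 per branch, 9 settings. From section 2.7: two arms, 1:1. From section 2.13: two-tailed tests. The effect size is taken as given.

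**Formulas (exact noncentral t).**
- One sample: df = n − 1, noncentrality = d√n.
- Two samples, n per arm: df = 2n − 2, noncentrality = d√(n/2).
- Power is the probability that the noncentral t exceeds the critical value at 1 − 0.05 (one-tailed) or 1 − 0.025 (two-tailed). The opposite tail is negligible here.

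**Step 1. Reproduce the plan's figure with the module it names.**

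| One-sample, d = 0.5 | n | Noncentrality | Critical t | Power |
|---|---|---|---|---|
| One-tailed | 44 | 3.317 | 1.681 | 0.947 |
| One-tailed | 45 | 3.354 | 1.680 | **0.951** |
| Two-tailed | 45 | 3.354 | 2.015 | 0.907 |
| Two-tailed | 53 | 3.640 | 2.007 | 0.947 |
| Two-tailed | 54 | 3.674 | 2.006 | **0.950** |

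The stated 45 is exactly the one-tailed answer; two-tailed, the module returns 54. A one-sample Wilcoxon with efficiency 3/π under normality gives 47 (one-tailed) or 57 (two-tailed). No two-tailed and no two-sample variant that was tried comes within two participants of 45.

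**Step 2. The randomised comparison, two-tailed, d = 0.5.**

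| n per arm | Noncentrality | Critical t | Power |
|---|---|---|---|
| 45 | 2.372 | 1.987 | 0.650 |
| 60 | 2.739 | 1.980 | 0.775 |
| 104 | 3.606 | 1.972 | 0.948 |
| 105 | 3.623 | 1.971 | **0.950** |

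So 95% power needs 105 evaluable per arm, and 105/45 = 2.3 times the stated minimum. Even one-tailed, the two-sample test needs 88 per arm.

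**Step 3. The pooled target.** 1080/2 = 540 per arm. At d = 0.5 the noncentrality is 0.5 × √270 = 8.22, and power exceeds 99.9%. If 25% dropped out (an assumption: 1 − 45/60; the article gives no rate), 540 × 0.75 = 405 per arm remain, and power at d = 0.5 still exceeds 99.9%.

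**Step 4. Effect detectable with 95% power, two-tailed.** Solving the two-sample formula for d:
- 45 per arm: 0.77
- 60 per arm: 0.66
- 405 per arm: 0.25
- 540 per arm: 0.22

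Normal-approximation check at 540: (1.960 + 1.645) × √(2/540) = 0.219.

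**The case against.** **The module may have been meant for the within-arm test.** Sections 2.12 and 2.13 plan a before-and-after CSSRS comparison in each group, and a one-sample calculation with n per branch is coherent with that. Section 2.3 never says that its 95% refers to a between-arm test. This explains where the number came from but does not rescue it. Under the article's two-tailed rule, 45 per branch has 90.7% power for the within-arm test, and 95% needs 54. At the full 60 per branch the within-arm power is 96.8%, so on this reading the shortfall is small. A fall within one arm, however, cannot show that the safety plan caused it. Cohort 1 is enrolled within a month of a suicide attempt or self-injury, so scores may fall in both arms.

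**The total is more than large enough.** This stands for the pooled comparison. Three settings with 45 completers per arm each (135 per arm) already give 98% power at d = 0.5.

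**Work by centre is already exploratory.** This also stands. Section 2.3 repeats the unit to explore bias between centres, and section 2.13 plans no efficacy test by centre.

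**The tail is not stated.** Correct. One-tailed use is inferred from the exact match at 45 and the gap of nine participants to the two-tailed answer.

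A reader might infer that the trial as a whole is underpowered, or that a null result in a single centre will be presented as well powered. The documents support neither: the recruitment target far exceeds 105 per arm, and no such centre-level test is planned.

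**Conclusion.** The power statement in section 2.3 is wrong as written and should be corrected. The named module does not fit a two-arm trial, and its answer of 45 agrees with the two-tailed rule in section 2.13 on no reading. For the between-arm comparison at d = 0.5, the stated 95% is really 65% at 45 per arm and 78% at 60 per arm without dropout; 95% needs 105 evaluable per arm.

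The consequence is limited. The fault is in the documented basis for the sample size and in the power of each 120-participant setting, and does not extend to the pooled comparison if recruitment comes near its target.

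These conclusions take d = 0.5 from the article and use an independent two-sample t-test. The pooled figures also assume one common effect across the clinical and student cohorts. The 405 per arm rests on a 25% dropout rate that 45/60 suggests but the article does not state.

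**What to change.** In section 2.3:

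- Replace the one-sample calculation with the difference between two independent means, two-tailed: 105 evaluable per arm for d = 0.5, 5% alpha and 95% power. Delete the claim of 95% power at 45 per branch.
- Name the pooled between-arm comparison as the powered one. Give its power at d = 0.5 (over 99.9% at 540 per arm) and its detectable effect at 95% power: d about 0.22 at 540 per arm, or about 0.25 at 405 per arm if dropout is 25%. The sponsor must confirm or replace that rate before it is written in.
- Beside the exploratory centre analysis, give each setting's between-arm power at d = 0.5: 78% at 60 per arm, 65% at 45.

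In sections 2.12 and 2.13, make the test of the main CSSRS outcome a between-arm comparison and keep the within-arm Wilcoxon test as supportive. Without this, the corrected sample size would refer to a test that is not the one planned for the main outcome.

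The cost is a text change in three sections and no extra participants. The drawback is that the stated power per setting becomes less favourable.

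### Stratifying by centre is the only reason given for 1080 participants, but neither the allocation rule nor the analysis section mentions centre or cohort

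*Protocol article*

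**What the plan says.** **Sample size (section 2.3).** A minimum of 45 per branch is raised to 60, or 120 in total. The article aims for that number in every hospital and in the educational settings, giving 120 × 9 = 1080. The reason given for the multiplication is: "In order to stratify by center—so that we can explore the possibility of bias by different recruitment centers". The target is hedged as something the team will try to reach.

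**Sites (sections 2.2.1 to 2.2.3).** The clinical cohort comes from "seven hospitals located in the three Spanish regions of Madrid, Andalusia, and Asturias". The high-school cohort consists of "adolescents aged 13 to 17 from ten secondary schools in the city of Madrid". The third cohort comes from one university.

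**Allocation (section 2.7).** "A 1:1 randomization will take place after enrollment". No stratum, block or centre is named.

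**Analysis (section 2.13).** The section lists t-tests, ANOVA, chi-square tests, a Wilcoxon test on the CSSRS score, Kaplan–Meier curves, and logistic regression adjusted for age and sex. As examples of possible confounders it gives other health apps on the phone and response latency. Section 3 adds covariance analysis for baseline differences. Neither section mentions centre or cohort.

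**The concern.** A design feature that sets the size of a trial should be traceable through the plan: from the sample-size paragraph to the randomisation and then to an analysis that uses it. Here it appears in the first place only.

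Two things are at stake. First, a team that follows section 2.13 as written would compare the arms across pooled cohorts that differ by design: patients with a suicide attempt or self-injury in the past month, screen-positive pupils aged 13 to 17, and screen-positive students aged 18 to 24. Baseline risk will differ between these groups, and the named tests do not account for that. Second, the centre-bias question would have no planned answer, although it is the stated reason for nine times as many participants.

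The word centre is also loose. Section 2.3 counts nine units, while sections 2.2.2 and 2.6 use the word for individual schools. The article does not say at which level the centre question will be asked.

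**Working it through.** **1. Reproduce the plan's figures.** The inputs from section 2.3 are a standardised effect ("we estimate an effect size of 0.5"), alpha 5%, power 95% and a one-sample t-test.
- Exact noncentral-t calculation, one-sided: n = 45, power 0.951. This matches the stated minimum. The two-sided version gives 54. That difference is a separate matter and is not pursued here.
- 45 / (1 − 0.25) = 60 per branch. No dropout rate is given; 25% is what the two figures imply.
- 2 × 60 = 120, and 120 × 9 = 1080. The centre argument therefore adds 1080 − 120 = 960 participants.

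**2. Where nine comes from.** Section 2.3 does not itemise it.
- Seven hospitals + one high-school setting + one university = 9.
- With each school counted separately, 7 + 10 + 1 = 18, and the same rule would give 120 × 18 = 2160.
- At 1080, the high-school unit has 120 / 10 = 12 per school, or 6 per arm, assuming equal recruitment.

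**3. What each level can support.** Two-sided between-arm t-test at 5%, effect 0.5 SD:

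| Level | Per arm | Power |
|---|---|---|
| Whole trial | 540 | > 0.999 |
| One unit of 120 | 60 | 0.775 |
| One unit, 25% lost | 45 | 0.650 |
| One school | 6 | 0.123 |

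Difference in treatment effect detectable with 80% power (normal approximation, multiplier 1.96 + 0.84 = 2.80):
- One unit against the other eight pooled: SE = √(2/60 + 2/480) = 0.194, so about 0.54 SD.
- Two units of 120: SE = √(4/60) = 0.258, so about 0.72 SD.
- Two schools of 12: SE = √(4/6) = 0.816, so about 2.3 SD.

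Between hospitals, the exploration can detect differences about as large as the planned effect itself. Between schools it is uninformative.

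**4. Imbalance if allocation were simple.** This is an assumption, because the article names no method. The number in one arm is then Binomial(n, 0.5).
- n = 120: SD = √120 / 2 = 5.48 and the 95% range is 49 to 71. A 50:70 split or worse has probability 0.082 in one unit, and 1 − (1 − 0.082)⁹ = 0.54 for at least one of nine.
- Cost in power within a unit: 0.775 at 60:60, 0.764 at 50:70, 0.761 at 49:71.
- n = 12: a 9:3 split or worse has probability 2 × (1 + 12 + 66 + 220) / 4096 = 0.146, and 1 − (1 − 0.146)¹⁰ = 0.79 for at least one of ten schools.

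**The case against.** The best defence is that the sections are compatible. A 1:1 allocation stratified by centre satisfies both 2.3 and 2.7, and a journal article may leave strata and block sizes to the full protocol. This stands. A reader might infer that randomisation is unstratified, but section 2.7 gives a ratio and a time and says nothing on method, and section 2.3 states an intent to stratify.

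A reader might also infer that centres will end up with badly unbalanced arms. For the hospitals and the university the figures do not support that: even simple allocation costs about one point of power in a unit of 120. Marked imbalance is plausible only within single schools, where it would affect about 12 of 1080 people at a time.

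A third tempting reading is that nine is a miscount for 18. It is not. Section 2.3 defines its units as hospitals plus educational settings, and nine fits that definition. Nor does the article document that pupils share the app across arms, and blocking within schools would not prevent it.

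Finally, centre can be fitted in the analysis whether or not allocation was stratified, and the confounders in 2.13 are introduced as examples, so centre is not excluded. That is true. But the section does name tests and factors, and it omits the one factor on which the sample size was justified. ANOVA is listed for comparisons of several groups, but no grouping by centre is given.

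**Conclusion.** The point holds as a mismatch between three sections: the purpose behind 960 of the 1080 participants is stated in 2.3 and is not taken up in 2.7 or 2.13. It does not invalidate the trial. The pooled comparison with 540 per arm keeps ample power for the assumed effect, and chance imbalance in the larger units is minor.

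What is lost is the planned use of centre. The stated tests ignore a factor that probably bears on outcome, and no centre-by-arm analysis is named. Between individual schools the centre-bias aim cannot be met at about 12 participants each. Between the nine units it can be met only for large differences, about 0.54 SD for one unit against the rest.

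The assumptions are equal recruitment across schools, full recruitment to 120 per unit and, for the imbalance figures only, simple randomisation.

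**What to change.** - **Section 2.7:** state that the 1:1 allocation uses permuted blocks of varying size within centre, with at least the nine units of section 2.3 as strata. Individual schools may be separate strata.
- **Section 2.13:** include centre as a stratum or covariate in the between-arm comparison, in place of the unadjusted tests, and name the exploratory centre-by-arm analysis.
- **Section 2.3:** say what counts as a centre, and limit the centre-bias aim to the seven hospitals and the three cohorts.

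The cost is a randomisation list set up this way before the first allocation and a few sentences of text. If allocation is already stratified in the full protocol, only the text changes. No extra participants are needed. The one small downside is some incomplete blocks if schools are separate strata.
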